### Summary:

Breast cancer (BC) is a major health problem and the most prevalent cancer among women. In a substantial proportion of familial cases, germ-line mutations in either BRCA1/2 can be detected. The only proven modality for active risk reduction (rather than passive early detection), is prophylactic surgery - prophylactic mastectomy and oophorectomy. While the majority of Jewish mutation carriers elect to undergo prophylactic oophorectomy at about age 40 years, in Israel only a minority perform prophylactic mastectomy. Another ramification of being a mutation carrier is the emotional stress associated with that discovery. Genetic information has profound implications for mutation carriers. The IBSR (Inquiry-based stress reduction) intervention, developed by Byron Katie, trains participants to reduce their perceived level of stress by self-inquiry of their thoughts and beliefs connected to stressful circumstances or symptoms. This meditative process, named "The Work", enables the participants to identify and question the stressful thoughts that cause their suffering. The core of IBSR is simply four questions and a turnaround, which is a way of experiencing the opposite of what the participant believes. This process is simple, powerful and provides skills for self-inquiry and management of stressful thoughts that can be easily implemented in daily life. Therefore, on the basis of previous data and beneficial observations we postulate that the clinical utility of IBSR mediation program may improve psychological and physical symptoms and quality of life among asymptomatic (oncologically healthy) BRCA1/ BRCA2 mutation carriers. Thus, we will conduct a pilot randomized controlled trial to scientifically investigate the effect of this intervention effects on BRCA1/2 mutation carriers.

### Study design:

Allocation: Randomized  
Intervention Model: Parallel Assignment

Masking: None (Open Label)  
Primary Purpose: Treatment

### **Arms and interventions:**

- **Experimental: Intervention**
  - Inquiry Based Stress Reduction
  - Intervention: Behavioral: Inquiry Based Stress Reduction (IBSR) program
  - Placebo Comparator: Control
  - The placebo group participants will receive book of IBSR intervention at the close of the study.
  - Intervention: Health Promotion–lifestyle modification: Control

### **Primary Outcome measures:**

**The Ryff scale- Psychological well-being-** quantified using the Ryff questionnaire (84-item). includes six subscales that evaluate: self-acceptance, positive relationships with others, autonomy, control of the environment, personal growth, and goals in life. For each of the dimensions, the score ranges from 14 and 84. Higher scores indicate higher psychological well-being.

### **Secondary Outcome measures:**

- **Sleep Quality** - assessed using the Pittsburgh Sleep Quality Inventory Questionnaire (PSQI) 19-items (score range 0-21) for self-reporting of sleep quality over one month.
- **Psychosocial variables (exploratory):**
  - positive and negative emotions (PANAS), a 20-item questionnaire (score range 10-50 for each subscale) that measures the emotional positive and negative state of individuals;
  - Satisfaction with Life Scale (SWLS), 5-item scale (score range 7-35) that measures global life satisfaction; self-assessed health (SAH), a single question designed to assess how the participant evaluates their health;
  - Perceived Social Support from Family (PSSFA), 20-item scale (score range 0-20) that assess the family support as perceived by the respondents;
  - mindfulness (MAAS), 15-item scale (score range 15-90) that measure level of attention and mindfulness to the present;
  - Life Orientation Test-Revised (LOT-R), 10-item questionnaire (score range 0-24) that measures optimism as a character trait, expected to remain stable throughout one's lifetime
  - General self-efficacy (GSE), 10-item scale that measures the general perception of personal agency in order to forecast the individual's ability to cope with everyday distresses and assess their adaptation to stressful events.

- **Health behaviors:** evaluated by the attitudes towards and actual performance of risk reduction surgical procedures of the breasts and/or fallopian tubes and ovaries.

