### **Eligibility criteria**

Ages: 25 to 70.

Sexes: female.

- **Inclusion criteria:** Women who are carriers of one of the predominant Jewish mutations in BRCA1/2 genes, age 25-70 years, with no current or past history of cancer (except BCC), who are willing to sign an informed consent, and present mental clarity by the ability to comprehend and fulfill all the questionnaires.
- **Exclusion criteria:** Diagnosed with breast or ovarian cancer or any other cancer, risk reduction mastectomy, severe psychiatric diagnosis (e.g. bipolar disorder).

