### **Statistical Plan:**

An intention-to-treat analysis approach will be implemented for this trial, and all subjects will be included in the data processing. The similarity of baseline (T1) demographic characteristics of participants in the control and intervention groups will be assessed using the Chi-squared test for categorical variables and independent samples t-test for continuous variables. Differences between the groups will be tested using mixed model analysis over the three different time points as well as the interaction between group and time. The dependent variables is the study outcomes, and the independent variables are time (before, immediately post-intervention, and during the follow-up period), group (intervention and control), and interaction between the time X the group. The difference between the outcome variables will be measured using the entry values (time point 1) and the final values gathered at the end of the follow-up (time point 3). Control for multiple comparisons will be done using the False Discovery Rate approach. An analysis of the research hypotheses of the categorical variables and variables without normal distribution will be performed according to the General Estimated Equation (GEE). To check the internal consistency of the research tools, an alpha Cronbach coefficient test will be performed for each tool. The statistical software SPSS 26 (IBM, New York City) will be used independently for all the data processing within this study by two researchers.

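### The surgery outcome has no time window or at-risk set, and for mastectomy the planned time-by-group term has no finite estimate under a logit link

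*Combined protocol and SAP*

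**What the plan says.** Under Secondary Outcome measures, the health-behaviour item covers attitudes towards surgery and "actual performance of risk reduction surgical procedures of the breasts and/or fallopian tubes and ovaries". It gives no window (ever, or since randomisation), does not say whether breast and ovarian surgery are scored separately, and does not require the organ to be present at entry.

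The exclusions under Eligibility criteria read "Diagnosed with breast or ovarian cancer or any other cancer, risk reduction mastectomy, severe psychiatric diagnosis". Prior oophorectomy or salpingo-oophorectomy is not among them, and ages run from 25 to 70.

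The Summary says that "the majority of Jewish mutation carriers elect to undergo prophylactic oophorectomy at about age 40 years", whereas "in Israel only a minority perform prophylactic mastectomy".

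The Statistical Plan includes all subjects and assigns categorical outcomes to GEE, with no link function named. It specifies that "the independent variables are time (before, immediately post-intervention, and during the follow-up period), group (intervention and control), and interaction between the time X the group", and it measures the outcome difference from time point 1 to time point 3. Surgery has no rule of its own.

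**The concern.** The outcome definition, the eligibility criteria and the model do not fit together, and they fail differently for the two organs.

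- **Ovaries and tubes.** By the protocol's own account of uptake and age, a good number of women may enter already operated on. They cannot have the ovarian event, yet nothing removes them from the analysis. Any effect on new surgery is averaged over women in whom it is impossible.
- **Breast.** No randomised woman can have had a risk-reducing mastectomy at T1. A model whose effect is a change from T1 then has a baseline with no variation. On the log-odds scale that baseline is minus infinity.

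At stake is the one outcome that records what women actually did. As written, the analyst must decide after seeing the data what counts as an event and who is in the denominator. If the stated model is followed with a logit link, the mastectomy result is unusable.

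**Working it through.** The documents give no sample size, event rate or effect size, so there is no figure of theirs to reproduce. The T1 mastectomy count of zero follows from eligibility. Arm size, event counts, surgery rates and prior-surgery shares below are assumptions for illustration.

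**1. Mastectomy, logit link**

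The T3-by-group term is

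[logit p(T3, intervention) − logit p(T1, intervention)] − [logit p(T3, control) − logit p(T1, control)].

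With p(T1) = 0 in both arms, each T1 logit is log(0/1) = −∞. The expression has no finite value at any sample size.

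To see what software does, take 50 women per arm with mastectomies (control/intervention) of 0/0 at T1, 1/2 at T2 and 3/6 at T3, and fit time, group and their interaction by GEE:

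| Model | Intercept (SE) | T3 × group (SE) |
|---|---|---|
| Logit, independence | −26.6 (903) | 0.76 (1,119) |
| Logit, exchangeable | −34.5 (about 2.1 million) | 0.86 (about 7.7 million) |
| Identity, independence | 0 (not computed) | 0.06 (0.057) |

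The software reported convergence in every case. The huge standard errors are artefacts of separation, not measures of effect; they show only that the term is not estimable.

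The identity-link value is the T3 risk difference: 6/50 − 3/50 = 0.06, with SE √(0.12×0.88/50 + 0.06×0.94/50) = 0.057. T1, constant at zero, adds nothing.

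Dropping T1 and keeping the logit link also gives finite results: group at T2 0.71 (SE 1.24) and T3 × group 0.05 (SE 1.03).

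**2. Oophorectomy, dilution**

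Let b be the share already operated on at entry, equal in both arms. Assume new surgery of 10% versus 20% among women still at risk. Ever-operated status at T3 is b + (1 − b)p, so the difference between arms is (1 − b) × 0.10.

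| b | Ever-operated at T3 | Difference | n/arm, T3 status alone | n/arm randomised, at-risk women only |
|---|---|---|---|---|
| 0 | 10% v 20% | 10 points | 199 | 199 |
| 0.2 | 28% v 36% | 8 points | 533 | 249 |
| 0.4 | 46% v 52% | 6 points | 1,089 | 332 |
| 0.6 | 64% v 68% | 4 points | 2,201 | 498 |

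Sample sizes are for 80% power at two-sided 0.05, from n = [1.96√(2p̄(1−p̄)) + 0.8416√(p₀(1−p₀) + p₁(1−p₁))]² / (p₁ − p₀)². The last column is 199/(1 − b), rounded up.

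**3. How much the T1 term rescues**

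The fourth column ignores T1, which the plan does not do. If each woman's change in status from T1 to T3 is compared, prior surgery counts as no change and the proportions become (1 − b) × 10% and (1 − b) × 20%. The same formula gives 258, 356 and 553 per arm for b = 0.2, 0.4 and 0.6. Most of the lost precision returns, but the difference is still only 8, 6 or 4 points.

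The logit model behaves alike. With ever-operated counts of 20/20, 21/22 and 23/26 out of 50, it fits and gives T3 × group 0.24 (SE 0.23). The same new operations among the 30 at-risk women per arm (3 v 6) give log[(6/24)/(3/27)] = 0.81, with SE √(1/6 + 1/24 + 1/3 + 1/27) = 0.76. The ratio of estimate to SE is similar (about 1.0 and 1.1), but the odds ratio is 1.27 instead of 2.25.

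**The case against.** A reader might infer more than the documents support, in four ways.

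- **That the plan counts operations done before entry.** It does not say so; it fails to exclude them. If surgery is recorded as status at each visit, a woman operated on before entry shows no change from T1 to T3, so the planned contrast partly nets her out. Step 3 bears this out. What stands is the denominator: she cannot have the event, and the estimate is pulled towards no difference.
- **That breast and ovarian surgery are pooled into one yes/no variable.** The and/or wording may only list the procedures asked about. The point above does not depend on pooling.
- **That the stated model cannot be fitted to mastectomy at all.** No link is named, and an identity link gives a usable answer. The failure belongs to the logit link, the usual choice for a binary outcome. The plan does not steer the analyst away from it.
- **That the whole health-behaviour outcome is uninterpretable.** Attitudes are untouched by the estimability problem, and a status model for oophorectomy does fit.

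It can also be said that prevalence at each visit is a legitimate target even for an irreversible event, and that this is a secondary outcome of a pilot. Both are fair. They limit the weight of the point, but they do not supply the missing definition or make the logit interaction estimable.

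**Conclusion.** The point holds in this limited form. Two parts rest on the documents alone: the surgery outcome has no window and no at-risk set, and eligibility puts mastectomy at zero in both arms at T1. The mastectomy time-by-group term therefore has no finite estimate under a logit link, at any sample size. That conclusion is conditional on the link, which the plan leaves open.

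That a sizeable share of entrants has already had an oophorectomy is a reasonable inference from the Summary and the age range, but no figure is given. For assumed shares of 20% to 60%, a 10-point difference in new surgery becomes 8 to 4 points. The loss is mainly in the size and meaning of the estimate. The loss of precision is large only if T3 status is compared without regard to T1.

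This should be corrected before analysis. It does not affect the primary outcome.

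**What to change.** In the outcome section and the Statistical Plan, replace the single surgery item with two outcomes, both counted from randomisation:

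1. new risk-reducing mastectomy, in all randomised women;
2. new risk-reducing salpingo-oophorectomy, in randomised women with ovaries or tubes in place at T1.

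Compare the arms once for each, on cumulative occurrence by T3. Report a risk difference with its interval and use an exact or Firth-type method, since the Summary suggests mastectomies will be few. State that these two outcomes are not analysed by the time-by-group GEE. Because organ status at T1 precedes randomisation, restricting the second analysis in this way keeps the randomised comparison.

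The cost is a few sentences, one baseline field for ovarian and tubal status, and a smaller denominator for the second outcome. Confirm that the chosen method is available in the software named in the plan. Restricting the attitude analysis to women still at risk of the operation concerned is optional.

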### **Eligibility criteria**

Ages: 25 to 70.

Sexes: female.

- **Inclusion criteria:** Women who are carriers of one of the predominant Jewish mutations in BRCA1/2 genes, age 25-70 years, with no current or past history of cancer (except BCC), who are willing to sign an informed consent, and present mental clarity by the ability to comprehend and fulfill all the questionnaires.
- **Exclusion criteria:** Diagnosed with breast or ovarian cancer or any other cancer, risk reduction mastectomy, severe psychiatric diagnosis (e.g. bipolar disorder).

### **Statistical Plan:**

An intention-to-treat analysis approach will be implemented for this trial, and all subjects will be included in the data processing. The similarity of baseline (T1) demographic characteristics of participants in the control and intervention groups will be assessed using the Chi-squared test for categorical variables and independent samples t-test for continuous variables. Differences between the groups will be tested using mixed model analysis over the three different time points as well as the interaction between group and time. The dependent variables is the study outcomes, and the independent variables are time (before, immediately post-intervention, and during the follow-up period), group (intervention and control), and interaction between the time X the group. The difference between the outcome variables will be measured using the entry values (time point 1) and the final values gathered at the end of the follow-up (time point 3). Control for multiple comparisons will be done using the False Discovery Rate approach. An analysis of the research hypotheses of the categorical variables and variables without normal distribution will be performed according to the General Estimated Equation (GEE). To check the internal consistency of the research tools, an alpha Cronbach coefficient test will be performed for each tool. The statistical software SPSS 26 (IBM, New York City) will be used independently for all the data processing within this study by two researchers.

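### No deciding contrast is named for the primary outcome, and the group test over three visits averages in the pre-treatment visit

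*Combined protocol and SAP*

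**What the plan says.** The Statistical Plan is one paragraph. On the treatment effect it gives three elements:

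- **(a) Group difference, and (b) its interaction with time, in one sentence:** "Differences between the groups will be tested using mixed model analysis over the three different time points as well as the interaction" of arm with visit.
- **(c) T1–T3 difference:** the outcome difference is "measured using the entry values (time point 1) and the final values gathered at the end of the follow-up (time point 3").

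The baseline visit is part of the modelled outcome, because "the independent variables are time (before, immediately post-intervention, and during the follow-up period), group (intervention and control"), plus their interaction. T1 is not described as a covariate. The Study design section states "Allocation: Randomized". On multiplicity the plan says only "Control for multiple comparisons will be done using the False Discovery Rate approach", with no family of tests and no level. The Primary Outcome measures section names the Ryff scale without a time point or a contrast.

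**The concern.** The three elements answer different questions. (a) compares the arms averaged over visits, one of which precedes treatment. (b) asks whether the arm difference changes at all across three visits. (c) looks only at the first and last visits. Nothing in the plan ranks them, so whether the intervention is judged to work can depend on which line of output is read. If the choice is made after the data are seen, it can follow the result.

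Element (a) has a defect of its own. Randomisation makes the expected arm difference at T1 zero, so including T1 in the group average mixes a visit that carries no treatment information, only chance imbalance, into the estimate.

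**Working it through.** The plan states no sample size, power, alpha or effect size, so there is no figure of its own to reproduce.

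**1. What the group effect estimates (from the design alone).** Let d2 and d3 be the true arm differences at T2 and T3. The T1 difference is expected to be 0. With equal weight on visits, the group effect is (0 + d2 + d3)/3. The average post-treatment effect is (d2 + d3)/2. The ratio is (1/3)/(1/2) = 2/3, whatever the pattern. Against the T3 effect the ratio depends on the pattern:

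- d2 = d3: 2/3
- d2 = d3/2: (d3/2 + d3)/3 = d3/2, ratio 1/2
- d3 = d2/2: (d2 + d2/2)/3 = d2/2 = d3, ratio 1
- d3 = 0: the group effect is d2/3 although nothing remains at T3

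If the group coefficient is instead read from a model with baseline as the reference visit, it is the T1 difference and carries no treatment effect.

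**2. Power (assumed inputs).** Assume n = 50 per arm, 1:1 allocation, SD 1, equal between-visit correlation r, complete data, two-sided 0.05, a true effect of 0.5 SD at T2 and T3, and a normal approximation.

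- Group effect: mean (0.5 + 0.5)/3 = 0.333, variance (2/n)(1 + 2r)/3
- T3 minus T1: mean 0.5, variance (2/n)·2(1 − r)
- T3 adjusted for T1: mean 0.5, variance (2/n)(1 − r²)

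At r = 0.6, with 2/n = 0.04:

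- Group: SE = √(0.04 × 2.2/3) = 0.171; 0.333/0.171 = 1.95; power about 49%
- T3 minus T1: SE = √(0.04 × 0.8) = 0.179; 0.5/0.179 = 2.80; power 80%
- Adjusted T3: SE = √(0.04 × 0.64) = 0.160; 0.5/0.160 = 3.13; power 88%

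| r | Group | T3 minus T1 | Adjusted T3 |
|---|---|---|---|
| 0.3 | 63% | 56% | 75% |
| 0.5 | 53% | 70% | 82% |
| 0.6 | 49% | 80% | 88% |
| 0.7 | 46% | 90% | 94% |

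For r from 0.5 to 0.7, the group test and the T3 minus T1 test disagree (one significant, the other not) in 49–53% of simulated trials.

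**3. Interaction when the effect is at T2 only.** The two changes from T1 have covariance (2/n)(1 − r) times the matrix with 2 on the diagonal and 1 off it. For d2 = 0.5 and d3 = 0, the noncentrality is (2/3)(0.5²)/[(2/n)(1 − r)]. At r = 0.6 this is 0.1667/0.016 = 10.4, which gives 83% power on 2 degrees of freedom (74–93% for r from 0.5 to 0.7). The interaction is then usually significant although the T3 effect is zero.

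**4. Null error from having three routes.** With no effect, (b) or (c) is significant in about 7.5% of trials. Under equal correlation the three-visit mean is independent of the within-person changes, so the chance that at least one of the three is significant is 1 − 0.95 × 0.925 = 0.12. Simulation gives the same 12%. If the Benjamini–Hochberg procedure at 0.05 covers the three tests, the chance of any rejection is about 4.5%.

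**The case against.** The strongest reply is that the plan describes one mixed model, and that the T1–T3 sentence says measured, not tested. It can fairly be read as naming the contrast of interest inside that model, with the interaction as its omnibus companion. On that reading only a clarifying sentence is missing. With (a) set aside and a 0.5 SD effect at both visits, (b) and (c) disagree in only 7–15% of trials (50 per arm, r 0.5–0.7). This reading is possible, but the plan does not state it. It also leaves in place the sentence that tests the arms over all three visits, and with an effect at T2 only (b) and (c) still disagree in 69–88% of trials.

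A reader might infer more than the documents support:

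- **That the T1–T3 measure breaks the intention-to-treat commitment.** The plan says "all subjects will be included in the data processing", and a raw change score exists only for women with a T3 value. But the plan does not specify a raw change score. Its stated method is a mixed model, which can keep women without a T3 value.
- **That the group test always shrinks the effect by a third or biases it towards zero.** The third is exact only against the average post-treatment effect under equal weighting. Against T3 it can be more, less or nil.
- **That the group test is always the weakest.** At r = 0.3 it has more power than T3 minus T1 (63% v 56%), though less than the adjusted T3 contrast (75%).
- **That the tests point in opposite directions.** They differ as significant versus not significant. Significant results of opposite sign occurred in at most 0.5% of simulated trials.
- **That error is 12% under the plan.** That holds only if FDR does not cover these tests, and the plan leaves this open.

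The trial calls itself a pilot, which lowers the stakes. It still tests hypotheses about the intervention's effect.

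**Conclusion.** The concern holds in this form: the plan names no deciding result for the primary outcome, and one of its listed tests, the group effect over three visits, is not a sound test of treatment. It estimates two-thirds of the average post-treatment effect under equal weighting, or no treatment effect at all under baseline-reference coding. This is more than missing detail, because following the sentence as written gives the wrong quantity.

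Only the two-thirds factor follows from the design, given randomisation and equal weighting. The power, disagreement and error figures illustrate the scale and rest on the assumed sample size, effect, correlation and complete data. In every setting shown with a lasting effect, the baseline-adjusted T3 contrast has the highest power of the three tabulated. The documents support neither a conflict with intention-to-treat nor an unconditional loss of a third at T3.

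**What to change.** Before outcome data are examined by group, replace the relevant sentences with one rule:

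- The deciding result for the primary outcome is the between-group contrast at T3 (1 degree of freedom) from the mixed model. T3 is the final time point the plan itself uses.
- Constrain the T1 means to be equal between groups, so that every randomised woman with any value is kept. Entering T1 as a covariate is an alternative, with the handling of women who have no later value stated.
- The T2 contrast and the omnibus interaction are supportive.
- The group main effect that includes T1 is not used as a test of treatment.
- State the family of tests to which FDR applies, and its level.

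The covariance structure should be stated, but no particular one is needed to resolve this point. The cost is SAP wording and a few lines of SPSS syntax, with no new data.

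### The mixed model has no baseline adjustment, so the T1-to-T3 group contrast is valid but less precise than it could be with scores already collected

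*Combined protocol and SAP*

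**What the plan says.** All of the analysis text is in the Statistical Plan section.

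- **Model.** Group comparisons come from one mixed model fitted to all three visits, with a group-by-time term. The listed terms are "the independent variables are time (before, immediately post-intervention, and during the follow-up period), group (intervention and control"), plus the product of the two. No baseline score or other covariate is named, and nothing says that the T1 means are held equal across arms.
- **Effect.** The difference in the outcomes is "measured using the entry values (time point 1) and the final values gathered at the end of the follow-up (time point 3").
- **Baseline comparison.** "The similarity of baseline (T1) demographic characteristics of participants in the control and intervention groups will be assessed using the Chi-squared test". Continuous characteristics get a t-test instead. No use of the results is described.

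Elsewhere, the Summary says "we will conduct a pilot randomized controlled trial", and the Study design section gives a randomised design with "Intervention Model: Parallel Assignment". The primary outcome is the Ryff questionnaire with six subscales: "For each of the dimensions, the score ranges from 14 and 84". The documents give no sample size, standard deviation, effect size, power or T1–T3 correlation.

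**The concern.** With T1 as a response and its group difference unconstrained, the T3-versus-T1 part of the interaction subtracts each woman's whole baseline score, which fixes the slope on baseline at 1. The best-fitting slope is normally below 1, so subtraction carries T1 noise into the comparison. A model that estimates the slope, or that uses the fact that randomisation makes the T1 means equal in expectation, avoids this.

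The stake is precision. A pilot trial is likely to be short of it, and six primary subscales under false-discovery-rate control add to the demand. The T1 scores are already collected, so the improvement needs no extra women and no extra visits.

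**Working it through.** The plan states no figure to reproduce, so the check is algebraic, with ρ as an assumption.

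**Inputs.** From the Statistical Plan: three time points, the three model terms, and the effect from T1 to T3. From Study design: randomised parallel arms. Assumed: n women per arm in a 1:1 ratio (the ratio is not stated and cancels below), a common variance σ² at T1 and T3, and ρ from 0.3 to 0.9.

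**Step 1: planned contrast.** One woman's change has variance 2σ²(1−ρ). The difference between two arm means therefore has variance (2/n)·2σ²(1−ρ).

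**Step 2: baseline-adjusted contrast.** Regressing T3 on T1 leaves residual variance σ²(1−ρ²), so the contrast has variance (2/n)·σ²(1−ρ²).

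**Step 3: ratio.** (1−ρ²) / [2(1−ρ)] = (1+ρ)/2. The reduction is 1 − (1+ρ)/2 = (1−ρ)/2. The standard error falls by 1 − √[(1+ρ)/2]. The extra sample that the planned contrast needs for equal precision is 2/(1+ρ) − 1.

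| ρ (assumed) | planned, 2(1−ρ) | adjusted, 1−ρ² | ratio | variance cut | SE cut | extra women needed |
|---|---|---|---|---|---|---|
| 0.3 | 1.40 | 0.91 | 0.65 | 35% | 19.4% | 53.8% |
| 0.5 | 1.00 | 0.75 | 0.75 | 25% | 13.4% | 33.3% |
| 0.7 | 0.60 | 0.51 | 0.85 | 15% | 7.8% | 17.6% |
| 0.8 | 0.40 | 0.36 | 0.90 | 10% | 5.1% | 11.1% |
| 0.9 | 0.20 | 0.19 | 0.95 | 5% | 2.5% | 5.3% |

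**Step 4: check on the full three-time-point model.** Generalised least squares with complete data was run for the planned model and for the same model with a common T1 mean. At one woman per arm and σ² = 1, the variance of the T3-versus-T1 group contrast is 2.00 against 1.50 at ρ = 0.5, 1.20 against 1.02 at 0.7, and 0.40 against 0.38 at 0.9. The ratios equal (1+ρ)/2 under both a compound-symmetry and a banded covariance. So the planned contrast has exactly the change-score variance, and the constraint recovers the whole gain.

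**Step 5: small arms.** Estimating the slope multiplies the adjusted variance by about 1 + 1/(2n−4). With an assumed 20 per arm that is 1 + 1/36 = 1.028, and the net cut is 22.9%, 12.6%, 7.5% and 2.4% at ρ = 0.5, 0.7, 0.8 and 0.9. With 10 per arm the factor is 1 + 1/16 = 1.0625, and the net cut is 20.3%, 9.7%, 4.4% and −0.9%. At that size and ρ = 0.9 there is nothing to gain.

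**Step 6: unequal variances.** With standard deviations σ₁ and σ₃, planned minus adjusted variance is proportional to σ₁² − 2ρσ₁σ₃ + σ₃² − σ₃²(1−ρ²) = (σ₁ − ρσ₃)². This is never negative, so apart from the small-arm penalty the direction does not depend on equal variances. The table's percentages do.

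**The case against.** The best defence is that the plan already uses the baseline scores and that its estimate is sound. Both parts stand. The similarity tests cover demographic characteristics only, and T1 outcome scores enter as the first response and as the start of the T1-to-T3 difference. A reader might infer that the baseline is used only for significance tests; the text does not support that.

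A reader might also infer bias. If the arms differ at T1 by a chance amount δ, the change-score estimate is off by −(1−ρ)δ, conditional on δ, when the variances are equal. That averages to zero over randomisation, so the contrast is unbiased. Nor does every prognostic imbalance stay in the estimate: a characteristic that shifts T1 and T3 equally cancels from the change, and only predictors of change remain.

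The size is open to challenge too. A flat loss of 15–25% would need ρ between 0.5 and 0.7, which the documents do not give. For at least one scale a high ρ is plausible: the Secondary Outcome measures section describes the LOT-R as a stable trait, and at ρ = 0.9 the gain is only 5%.

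Last, the formula is for continuous outcomes. The plan sends categorical and non-normal variables to GEE, and with a logit link covariate adjustment changes the quantity being estimated. A covariate model of T2 and T3 alone would also leave out women with only T1 data, which sits badly with the plan's intention to include all subjects. These points limit the scope and shape the fix; they do not remove the efficiency gain.

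**Conclusion.** The concern holds as an efficiency point. As written, the T1-to-T3 contrast from the mixed model is a change-score contrast. For continuous outcomes, baseline adjustment would reduce its variance by (1−ρ)/2, which runs from 35% to 5% over ρ = 0.3 to 0.9. The size rests on an assumed ρ, equal variances at T1 and T3, and complete data, and it shrinks somewhat in small arms.

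The documents do not support calling the planned analysis invalid or giving one unconditional percentage. No power figure is offered, because the documents state neither an arm size nor an effect size. The baseline p-values answer no useful question in a randomised trial, but the plan ties no decision to them, so they change no result. Nothing suggests that covariates would be chosen by those tests.

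**What to change.** For the continuous outcomes analysed by mixed model, the Ryff subscales first, choose one of these in the Statistical Plan:

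1. **Preferred:** keep the three-time-point model but constrain the T1 means to be equal across arms. Drop the group main effect and enter group only through its products with T2 and T3. An unstructured covariance lets the T1–T3 correlation be estimated freely. All randomised women with any outcome data are kept.
2. **Alternative:** model T2 and T3 with the T1 score of the same outcome as a covariate, and say how women with T1 data only are handled.

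In either case, name the group difference at T3 as the effect. Leave the GEE outcomes outside this change unless the target quantity for them is restated.

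Age is known at entry, as an eligibility item, and may be pre-specified as a covariate. Oophorectomy status should not be added unless the sponsor confirms that it is recorded at T1: ovarian surgery appears only within the health-behaviour outcome, with no collection time. Replacing the baseline p-values with a descriptive table is optional tidying.

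The cost is SAP wording, settled before the outcome data are examined, and a small degrees-of-freedom penalty that matters only if the arms are very small and ρ is very high. No new outcome data are needed.
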